#### Safety measures

All adverse events (AE) occurring after the date of consent are reported as AE and graded using criteria established by the National Cancer Institute (NCI) CTCAE version 5. Women who become pregnant during the trial will be advised to discontinue the intervention. Serious AE (SAE) must be reported to the study manager within 24 h of becoming aware of the event. Relapse and death due to breast cancer are not considered to be SAE. The reporting requirement for SAE applies for all events occurring up to 28 days after the last administration of study intervention. All unresolved AE will be followed by the study team until resolved, the participant is lost to follow up, or the AE is otherwise explained.

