### Randomisation

Eligible, consenting participants with complete baseline data are randomly allocated 1:1 to receive standard care (control) or the YWWACP intervention in the electronic data capture system used by Cancer Trials New Zealand (CTNZ). Randomisation should take place within 14 days after registration. The web-based randomisation process is carried out by a member of the research team who is independent of recruitment and data collection. Randomisation is blocked over time, using random block sizes to aid concealment of allocation. This is a single-blinded study, where only the research assistant (RA) is blinded to the assigned treatment. The RA instructs participants on how to conduct waist measurements at baseline (*T*_0_), weeks 12 (*T*_1_), and 24 (*T*_2_) and is blinded to ensure no influence of group allocation on instructions given. No other study investigators are blinded. This means emergency unblinding is not required.

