The hardcopy book brings together lifestyle information to assist with commencing and/or maintaining a balanced lifestyle following treatment for breast cancer. It includes a week-by-week, stepped program divided into four main components [(1) changing lifestyle; (2) maintaining habits, (3) healthy screening, and (4) moving forward]. The book is used alongside the virtual consultations with the cancer nurse specialist and the program journal. The program journal provides all necessary health promotion content and supports participants to log relevant health and lifestyle information into the journal. A weekly physical activity planner encourages participants to plan ahead for their physical activity in the following week. The interactive website incorporates news and announcements; new evidence; an online moderated ‘community’ allowing participants to communicate with each other; and an overview of the program. The website is adapted for all computing platforms, including smartphones and tablet devices.

Three consultations with a cancer nurse specialist trained in the intervention are conducted via videoconferencing. In keeping with privacy guidelines, no recording of the consultations is undertaken. The nurse specialist measures intervention adherence at the consultations as well as resources accessed at weeks 12 (*T*_1_) and 24 (*T*_2_).

Modification of the intervention is permitted if deemed necessary by the trained nurse specialist at any time during the intervention period. The reasons for modifications are captured. Discontinuation of the intervention can occur if the lead investigator decides the participant is at risk (e.g. serious medical condition, pregnancy), if the participant is unable to complete the program or fails to comply, and/or if the participant withdraws their consent. Reasons for discontinuation of the intervention are recorded.

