### Standard care

Participants allocated to the standard care group receive general information from their usual health professionals during routine clinic visits about the management of all symptoms. This includes general advice available regarding physical activity, diet, tobacco and alcohol abstinence, plus information about support services such as Pinc & Steel (physiotherapy and exercise) and the Divisions of the Cancer Societies in Aotearoa/New Zealand, and Cancer Council Queensland in Australia. Participants’ use of these services, and any interventions they offer, are recorded. Control participants are offered a hard copy of the YWWACP book on completion of the study.

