### Outcome measures

The feasibility study collects both the efficacy outcome measures for the planned phase III trial (in order to test feasibility) as well as specific feasibility study outcome measures. There are three data collection time points; baseline (*T*_0_), 12 weeks (*T*_1_), and 24 weeks (*T*_2_). A window of up to 14 days is allowed for *T*_1_ and *T*_2_ (Fig. 2).

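### SAE reporting ends at a date set by receipt of the intervention: control women have no such date and discontinuation brings it forward, so equal SAE ascertainment between arms is not assured

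*Protocol article*

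**What the plan says.** Under Safety measures, adverse event reporting begins at consent and is not limited by arm: "All adverse events (AE) occurring after the date of consent are reported as AE". No end date is given for it. Serious events carry a faster duty: "Serious AE (SAE) must be reported to the study manager within 24 h of becoming aware of the event". That duty is then limited in time: "The reporting requirement for SAE applies for all events occurring up to 28 days after the last administration of study intervention". The section gives no other end point for SAEs. Events still open are kept under observation: "All unresolved AE will be followed by the study team until resolved, the participant is lost to follow up, or the AE is otherwise explained".

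Under Randomisation, women are "randomly allocated 1:1 to receive standard care (control) or the YWWACP intervention". The Standard care section describes the control condition: "Participants allocated to the standard care group receive general information from their usual health professionals during routine clinic visits". The only programme material it offers controls is the book, once their study participation has ended.

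The Intervention section sets a 12-week programme, and Table 2 places nurse consultations at weeks 1, 6 and 12. The programme can be stopped early, among other reasons because the lead investigator judges a woman to be at risk. "Reasons for discontinuation of the intervention are recorded". Under Outcome measures, "There are three data collection time points": baseline, week 12 (T1) and week 24 (T2), with no distinction by arm.

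**The concern.** A reporting window in a two-arm trial should close at a date that can be worked out for every randomised woman in the same way. This one closes at a date that depends on receiving the programme. Half the women are allocated not to receive it, so staff must supply a rule for them that the article does not contain. Two coordinating centres run the two trials and could supply different rules, although the Background section says the trials are meant to harmonise methods so that outcomes can be pooled.

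In the intervention arm the rule can be applied, but the window shortens as exposure shortens. A woman taken off the programme early because she is at risk has the shortest SAE window, although her later course is of particular interest for safety.

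At stake is whether SAE counts in the two arms can be read side by side. The studies are also described as following the planned phase III methods, so an unworkable window is best corrected before a larger trial is written.

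**Working it through.** The plan gives no SAE figure to reproduce, so the check applies the stated rule to each arm.

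**Inputs.** Window: 28 days after last administration (Safety measures). Consultations: weeks 1, 6 and 12 (Table 2), taken as days 7, 42 and 84. Last planned assessment: week 24, day 168 (Outcome measures). Planned size: 60 per arm over both trials (Abstract).

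**Intervention arm.** Window end = day of last administration + 28. This assumes that the last consultation attended is the last administration.
- Last contact week 12: 84 + 28 = day 112 (week 16), which is 112/168 = 67% of follow-up.
- Last contact week 6: 42 + 28 = day 70 (week 10), 70/168 = 42%.
- Last contact week 1: 7 + 28 = day 35 (week 5), 35/168 = 21%.
- If the 14-day assessment window also delays the week 12 contact: 98 + 28 = day 126 (week 18).

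The assumption matters. The programme also includes a book, a journal and a website, and the nurse records resources accessed at weeks 12 and 24. The article does not say whether using these counts as administration.

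**Control arm.** The formula has no input, so no end date follows. Staff could adopt any of the readings below. Each is an assumption, and each ratio is the control window divided by the 112-day intervention window.
- No SAE window at all: 0/112 = 0.
- 28 days from randomisation: 28/112 = 0.25.
- A nominal 12 weeks plus 28 days: 112/112 = 1.00.
- To T2: 168/112 = 1.50.
- To T2 plus 28 days: 196/112 = 1.75.

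Among readings that give controls some window, the ratio runs from 0.25 to 1.75. It lies on both sides of 1 and includes 1.

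**Illustration in events.** Take one reading: controls reported to day 168, intervention women to day 112. Assume the same constant hazard in both arms and a 24-week risk r of at least one SAE. The article gives no SAE risk, so r is shown over a range. The expected number of women with a reported SAE in an arm of 60 is 60 × (1 − exp(−h × d)), with h = −ln(1 − r)/168 and d the window in days.
- r = 2%: 0.80 against 1.20.
- r = 5%: 2.02 against 3.00.
- r = 10%: 4.07 against 6.00.

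On that reading the window alone would add between about 0.4 and 1.9 women with an SAE to the control arm. The 28-day reading would reverse the direction, and the nominal reading would remove the difference.

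**The case against.** The strongest reply is that the reporting duty is not the same as capture. All adverse events after consent are reported and graded, without limit by arm and without an end date, and a serious event is also an adverse event. The 28-day sentence follows the 24-hour rule and most naturally limits that rule. A serious event in a control woman, or in week 20, would still fall under adverse event reporting. Unresolved events are followed, so the condition that took a woman off the programme is not dropped when her SAE window closes. This stands. It narrows the point to new events outside the window, which lose the SAE reporting requirement but need not go unrecorded.

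It also disposes of three stronger readings that a reader might infer. One is that serious events in controls go unrecorded, so that every reported SAE falls in the intervention arm. Another is that women who discontinue are lost to safety follow-up. The general adverse event rule contradicts both. The third is that controls would show about 1.5 times as many SAEs, flattering the programme. That needs controls to be reported to T2, which the article nowhere says.

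A second reply is that no planned result is affected. The only between-arm comparison named under Data analysis is waist circumference, and none of the feasibility criteria uses adverse events. This also stands, and it limits the importance of the point for these two studies.

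A third reply is that the full protocol or the centres' safety procedures, mentioned under Quality assurance, may settle the matter. They may, but nothing shown says that they override the stated sentence. The article does not leave the window to another document: it states one, and what it states cannot be applied to one arm. A nominal 12 weeks plus 28 days for everyone would give equal periods, but the text does not say that, and it would depart from the text for women who discontinue.

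**Conclusion.** The point holds in limited form. Followed literally, the SAE rule yields no end date for control women during the trial, and it yields an earlier one for intervention women who discontinue, including those stopped because they are at risk. Equal SAE ascertainment in the two arms is therefore not assured. The article does not support saying that ascertainment is in fact unequal, or in which direction: the control-to-intervention ratio of window lengths could be 0.25, 1.00 or 1.75, depending on a choice it leaves open. The week 16 closing date for women who complete the programme rests on treating the week 12 consultation as the last administration. The feasibility decision does not depend on SAEs. What is affected is the readability of SAE counts by arm, and the rule that a phase III protocol could take over.

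**What to change.** Replace the exposure-based end point with one calendar window anchored to consent or randomisation, identical in both arms and unaffected by receipt or discontinuation of the programme. For example: *SAEs are reported from consent to the week 24 assessment in both arms, whether or not the intervention was received or discontinued.* Consent would match the existing start of adverse event reporting. The length is for the sponsor to set; week 24 is offered because both arms are already assessed then. Add a short question about events to the online feasibility questionnaire that both arms complete at T1 and T2, so that the way of asking is also the same.

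The Discussion reports that Kōwhai finished its longitudinal assessments in September 2021, so the change can reach only EMERALD and the phase III protocol. Any pooled safety summary should state that Kōwhai used the exposure-based rule and how it was applied to controls.

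The cost is a sentence in the protocol, a questionnaire item, ethics approval of the amendment, and a few more events to report. The main drawback is that two trials described as identical apart from site details would have different SAE windows.

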### Quality assurance

The nurse specialist is fully trained in intervention delivery and adheres to documented policies and procedures. Case review by the study manager of at least one virtual consultation per month monitors adherence to study protocols, with the nurse completing a checklist at the end of each session to indicate the strategies used.

Oversight of the studies is provided by a single Trial Management Committee (TMC), which is responsible for funding and setup, ongoing study conduct, promotion of the study and the interpretation of results at both sites. Both studies have the same statistics and database team, and use the same data systems. The Kōwhai study is managed by the CTNZ trial coordinating centre and the EMERALD study is managed by the Wesley Choices Cancer Support Centre in conjunction with the Wesley Research Institute. Each trial coordinating centre follows standard operating procedures for safety reporting, and to ensure quality and adherence to Good Clinical Practice. Data management and statistical support is provided by CTNZ for both trials.

The RAs receive data collection training and are audited monthly. Participants who withdraw from the study are encouraged to provide follow-up data. Information on reasons for withdrawal are collected. Details for participant compensation as part of this trial are provided in the participant information sheets (provided in Additional files 1 and 2).

Data are entered into the e-PRO platform by the participant or by a member of the study team, as appropriate. Only specific research team members are authorised to access the electronic platform, using a unique user ID and a password. The system also promotes retention and follow-up as it emails reminders to the participants and alerts the research staff to study tasks (e.g. organisation of 12-week appointments).

### Data analysis

Analysis will follow standard approaches for descriptive analyses. For each trial, proportions, means and standard deviations (little skew), or medians and interquartile ranges (serious skew), will be reported as appropriate, and 95% confidence intervals will be provided for proportions and means/medians. Waist circumference will be compared in intervention and control arms using a linear mixed model with a treatment-time interaction. All analyses will be carried out in Statistical Analysis System (SAS) or STATA.

#### Sample size calculation

For each of the trials (Kōwhai and EMERALD) a sample of 60 patients was chosen so that proportions between 0.1 and 0.9 could be estimated with a margin of error < 0.13.

## Discussion

Women with breast cancer have been involved in the design (content and delivery method) of the intervention and the research method from conceptualisation. This included semi-structured focus groups with 16 women less than 2 years following acute treatment for breast cancer (< 40 years, *n* = 6; > 40 years, *n* = 10) [18] and a cross-sectional survey study in 85 women who had finished menopause-inducing cancer treatment at least three months prior (average age = 45 years; breast cancer = 54% of total sample) [19]. Twenty-two participants from the cross-sectional survey study (average age = 44 years; breast cancer = 41% of total sample) further participated in qualitative interviews [5]. This series of studies determined the content and format of the original WWACP. [name] is also a consumer representative highly trained in the conduct of clinical trials and has consistently advised from trial inception on all aspects of the study’s methodology, including the formulation of research endpoints, recruitment strategies and choice of outcome measures. The study methodology was tested in the Australian pilot, with feedback from participants indicating a significant survey burden (average 90 min to complete at each time point). As a result of this feedback, the survey instruments were changed to ensure that, while each construct is reliably and validly measured in the study described in this paper, the survey suite is much shorter (designed for an average 30 min to complete at each time point). Free text responses at week 12 (*T*_1_) will ask participants to provide their perceptions of the content of the new measurement suite and the time taken to complete it. In addition, the content of the intervention was initially developed after a series of focus groups with women with breast cancer and has been refined with their feedback from pilot work in both countries. In terms of conducting the study, consumer representatives in both study sites actively participate in the monthly TMCs. The study results will be disseminated to all participants at their request in a lay report, the content and format of which will be designed with the consumer representatives of the TMC.

A limitation of this study is participants needing to speak English, which could exclude some First Nations women or individuals from other language groups from participating in the Kōwhai or EMERALD studies. It should be noted, however, that we are currently working with Māori women (First Nations Aotearoa/New Zealand) and Cantonese women in Hong Kong to develop culturally adapted interventions and research protocols to ensure their culturally specific needs are addressed in further iterations.

There have been inevitable delays associated with COVID-19 lockdowns after receiving funding. We are fortunate that to date these have not had a significant impact in Aotearoa/New Zealand, where the study has been vigorously championed by our partners and enthusiastically received by the target group, even when an extended lockdown was ordered contemporaneous with study commencement. The Aotearoa/New Zealand study commenced in September 2020, 7 months after the intended start date in late February. Target baseline recruitment of 60 women was completed in March 2021 (consistent with our original timeline despite COVID-19); 12-week intervention delivery was completed in July 2021 and longitudinal assessments were completed in September 2021. We expect the same rapid uptake in the Australian site once it commences. Our preliminary work when developing this program indicated an enormous appetite for this type of intervention and we have the advantage in a research context dominated by COVID-19 that the intervention, consultation, and data collection procedures are entirely virtually delivered. In addition, the intervention is easily adapted to lockdown conditions, as it encourages creative and sustainable self-management of participants’ lifestyle concerns. The Australian feasibility study commenced in March 2022.

## Data Availability

As per funding body requirements, deidentified data may be made publicly available to other researchers subject to requirements of indigenous data sovereignty.

## Abbreviations

AE: Adverse events
ANZCTR: Australian New Zealand Clinical Trials Registry
ASIR: Age-standardised incidence rate
CI: Chief investigator
CTNZ: Cancer Trials New Zealand
e-PRO: Electronic patient-reported outcome
NCI: National Cancer Institute
NHMRC: National Health and Medical Research Council
PRO: Patient-reported outcome
RA: Research assistant
RCT: Randomised controlled trial
SAE: Serious adverse events
SAS: Statistical Analysis System
TMC: Trial Management Committee
WWACP: Women’s Wellness After Cancer Program
YWWACP: Younger Women’s Wellness After Cancer Program
